### Integral group

The intervention will be implemented by the CUIDATE research group. The supervised face-to-face program involves two parts (8 weeks in total). The participants will may use the BENECA System (mobile app) daily, which aims to recover a healthy lifestyle in BCS (in terms of energy balance: physical activity and dietary). On the second day of the assessment, staff will install the app on the participants’ mobile phones and will train them to use it. Furthermore, the women will receive telephone calls and text messages (as required) to resolve any questions and provide suggestions, and a video tutorial on how to use the application is also available on the web.

Moreover, participant will receive a supervised face-to-face rehabilitation program. This intervention consists of a supervised-occupational therapy rehabilitation program at the iMUDS centre (Mixed Institute University Sport and Health). Because there is no information about the ideal occupational therapy program for breast cancer patients, we have developed a comprehensive program that covers most of the physical, cognitive and emotional needs of these patients after oncology treatment from the occupational therapy perspective.

The second part is based on the fact that this span has been used in previous RCTs that have similar outcomes and samples [9, 18]. The occupational therapy program includes 3 weekly sessions of 60 to 90 min each. The weekly sessions will be distributed as follows: 2 sessions/week in a ROM-cognitive subprogram (approximately 50 min/session) using therapeutic workshops and individualized treatment that focus on improving the ROM, muscle strength and endurance, and manipulative skill and energy conservation as well as cognitive activities; 3 sessions/week of a psychomotricity program (approximately 45 min/session) including activities to improve functional capacity and address fatigue and pain as well as a warm-up period and relaxation techniques; and finally, 1 session/week of a psychosocial intervention (approximately 30 min/session), working on areas of ergonomics, techniques of energy conservation and fatigue management, job anxiety, coping techniques and occupational balance. All of these exercises will be assigned to women in the integral group according to their perceived needs at the baseline assessment. These needs will be established based on the fatigue levels, pain, functional capacity, ROM, and distress levels reported by the patients. Therefore, each participant will receive individual and progressive training (for example, the number and type of exercises, series, repetitions and so on). Efforts will be made to prevent the integral group from receiving additional physical care.

### M-HEALT: BENECA APP system

BENECA asks users to register their food and drinks and the different activities performed during the previous day. With an open structure and four time periods, the application will take the form of a questionnaire on the diet (over the last 24 h) and a record of daily activities in terms of duration and intensity. Users also record their weight (kg) and height (cm). After entering the information, the system will provide the patient information about their energy balance and general recommendations on physical activity according to their individual profile, using the reference guide for exercise in cancer patients from the American College of Sports Medicine [68]. Additionally, it provides recommended substitutions for foods that are considered potentially carcinogenic with others that may have a protective capacity against cancer, according to the guidelines of the American Cancer Society [11, 69] and the recommendations of the WCRF about the consumption of food of plant and animal origins, food with low energy density, etc. Furthermore, the program also detects the presence of an energy imbalance.

### Telephone calls

The CUIDATE group will make the telephone calls and send messages of encouragement. On the one hand, with this calls, participants will be able to solve any problems with the usage of BENECA app. Moreover, we will check the patients’ improvement and satisfaction. On the other hand, the aim of messages will be to stimulate not only the adherence with BENECA app but also with the program.

### M-Health group

Because it is a study of therapeutic superiority, the m-health group will use the BENECA app for 2 months and will receive some general recommendations about healthy lifestyle, stress management and occupational balance in paper format. After completion of this study, the m-health participants will be given the opportunity to participate in the supervised face-to-face program due to the ethical concerns of the CUIDATE group. The data obtained will be not used in this study.

### Data analysis

All analyses will be carried out using STATA/SE 14.0 StataCorp, College Station, TX, USA) or using Statistical Program for Social Sciences (IBM© SPSS© Statistic version 20, Corp., Armonk, NY). We will check the normal distribution of variables with Kolmogorov-Smirnov and Shapiro-Wilk test, as appropriate, and the differences at baseline between groups with Chi-square test or Student *t*-test, as appropriate. The main analysis will be repeated measures analyses of the covariance (ANCOVA) with age, type of surgery, tumour stage and time since diagnosis as covariates. Intergroup effect sizes will be calculated to provide change magnitude information. We will use the intention-to-treat principle for all analyses.

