### Research design and methods

The present study is a parallel group, assessor-blind, superiority RCT that will be conducted using assessments at baseline and immediately after the 8-weeks intervention. Follow-up measurements will be collected for 24 weeks after the end of the 8-week intervention period, resulting in a total trial data collection period of 32 weeks. We will use two separate assessment days to avoid fatigue in patients. In Table 1 is shown the study assessment schedule.

**Table 1 Tab1:** Study assessment schedule

Assessment	Baseline	Post-intervention (8 weeks)	Follow – up (24 weeks)
Informed Consent	x		
Day 1 testing			
Sociodemographic data	x		
Anthropometric data, pressure/rate heart	x	x	x
Accelerometry (1 week)	x	x	x
Body Composition (DEXA)	x	x	x
Minnesota	x	x	x
Self-efficacy Physical Activity questionnaire	x	x	x
EORTC QLQ-C30	x	x	x
EORT QLQ-BR23	x	x	x
Day 2 testing			
WAIS-IV^a^(subtest)	x	x	x
Trail Making Test (TMT)	x	x	x
Handgrip strength	x	x	x
Lymphedema	x	x	x
Hospital Anxiety and Depression Scale	x	x	x
DASH	x	x	x
Goniometry	x	x	x

^a^Working memory and processing speed subtest

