### Sample size

The sample size and power calculations for this trial were obtained through overall Health-Related QoL (HRQoL) using EORTC QLQ-C30 version 3.0 [40], and taking into account previously reported data [67] a minimally important difference from 5 to 10 points was considered. Assuming that integral group increase HRQoL in BCS in compared with m-health group [18] we can detect differences of at least 5% with a power of 90% and an α of 0.05 with two groups (Integral group and m-health group) of 36 participants assuming similar standard deviation (approximately 7 points). A maximum loss at follow-up of 10% will be allowed to face a possible drop-out rate [9]. Hence, we will recruit 80 BCS (40 in each group). Fig. 1 shows the flow diagram of the study participants.

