### Randomization and blinding

To reduce the risk of bias during the assessment, after completion of the baseline assessment we will allocate eligible patients randomly either m-health or integral groups into three randomization waves, using computer-generated numbers (EPIDAT 3.1, Xunta de Galicia). An external member will introduce the sequence in sealed opaque envelopes. Assessment staff will be blinded to patients’ randomization assignment and the staff responsible of the rehabilitation program will not be able to change any assignment. After the 6-month follow-up period, and because of ethical implications, once the last outcome variable has been measured we will invite participants of the m-health group to participate into the face-to-face rehabilitation program.

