## Discussion

This RCT will investigate whether there are clinically relevant differences in improvements in the QoL of BCS between an integral strategy and the use of the m-health system alone. This study has been designed to address the new needs for support and treatment of breast cancer survivors, reflecting the emerging need to merge new, low cost treatment options with the much-needed involvement of health professionals in the treatment of this type of patients. The supervised program includes not only strengthening and range of motion exercises of the shoulder, which are necessary in these patients [9], but also features a cognitive [25] and psychosocial [27] approach in a single intervention program which, together with the use of the m-health application [17], provides the integral character of the project.

In addition, most studies in cancer patients have been conducted with a rehabilitation team comprising nurses, psychologists and physiotherapists [8, 27]. For this reason, we chose to use a supervised face-to-face rehabilitation program conducted by an occupational therapist, due to the holistic and integrative approach of the discipline. Although we expect to see improvements in the primary outcome in both groups, we hypothesize that the combination of the supervised program and the m-health system will cause significant differences in QoL compared with the m-health group. QoL improvement is considered an indicator of cancer rehabilitation success [70]. If this integral option is effective, it will highlight the need for health systems to include disciplines such as occupational therapy in the supportive care of cancer patients during the survival period, as well as the potential advantage and cost reduction provided using a mobile app. Moreover, the results of this study could garner support for the use of this type of strategy in an increasing number of 17.8 million cancer patients in the European Union [71], with a high proportion of them claiming adequate rehabilitation services.

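### The main repeated-measures ANCOVA omits baseline QoL from its covariates and fixes neither the role of the baseline visit nor the tested term, at a cost in efficiency that depends on the reading

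*Protocol article*

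**What the plan says.** The Data analysis section of the protocol article gives the main analysis as "repeated measures analyses of the covariance (ANCOVA) with age, type of surgery, tumour stage and time since diagnosis as covariates". The list is explicit, and the baseline value of the outcome is not on it. The only use of baseline data that the section spells out is a check of "the differences at baseline between groups with Chi-square test or Student" *t*-test. It does not say whether the baseline visit is a level of the repeated factor, or whether the group main effect or the group-by-time interaction answers the main objective.

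Baseline QoL is available. Research design and methods plans "assessments at baseline and immediately after the 8-weeks intervention", with a further follow-up 24 weeks after the intervention ends, and Table 1 schedules both QoL questionnaires at all three visits. Randomization and blinding adds that "after completion of the baseline assessment we will allocate eligible patients randomly". Baseline QoL is therefore a pre-randomisation measurement and a legitimate covariate, and its expected difference between the arms is zero.

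The question is posed in points. Sample size takes 5 to 10 points as the minimally important difference, and the Discussion asks about "clinically relevant differences in improvements in the QoL of BCS".

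**The concern.** The sentence can be carried out in three ways, and each differs from an analysis that adjusts for baseline.

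- **(a) Only the post-baseline visits are outcomes.** Baseline QoL is then unused. With SD 7 and 36 per arm, the standard error of a chance baseline difference is 7 × √(2/36) = 1.65 points. An imbalance of 3 points is therefore quite possible, against a target of 5, and it would go uncorrected.
- **(b) Baseline is a level of the repeated factor and the group main effect is tested.** A visit with zero expected difference is averaged into the treatment effect.
- **(c) Baseline is a level of the repeated factor and group-by-time is tested.** Baseline is used and nothing is diluted. The test is, however, a 2-df omnibus test that is tied to neither later visit, and a significant result does not by itself say how many points separate the arms, or when.

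At stake are power, and a primary result that can be set directly against the 5 to 10 point threshold. If the tested term stays open, it can also be chosen after the data are seen.

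**Working it through.** **Inputs.** From Sample size: difference 5 (written as a percentage, read here as points on the 0 to 100 scale), SD about 7, 36 per arm analysed, α 0.05, power 90%. Not given: sidedness (two-sided assumed) and the correlation ρ between visits (assumed equal for all pairs, range 0.3 to 0.8). The test/retest reliability of 0.82 to 0.91 in the primary outcome section is not an 8-week or 32-week correlation and serves at most as an upper guide. The four listed covariates are ignored throughout.

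**The plan's own figure.** The section says "we can detect differences of at least 5% with a power of 90% and an α of 0.05 with two groups" of 36. With n = 2(z₁ + z₂)² SD²/δ²:
- two-sided: 2 × (1.960 + 1.282)² × 49/25 = 41.2, so 42 per arm;
- one-sided: 2 × (1.645 + 1.282)² × 49/25 = 33.6, so 34 per arm.

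The stated 36 is thus close to the one-sided result; two-sided it needs an SD of about 6.5. Inflation for dropout reproduces: 36/0.90 = 40 per arm. Sidedness is a separate matter. For the present point, 36 per arm gives two-sided power of 0.85 for one unadjusted visit (noncentral t; 0.86 by normal approximation).

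**Formulas**, with per-woman variance v and standard error √(2v/36):
- one later visit, unadjusted: v = 49;
- one later visit, baseline-adjusted: v = 49(1 − ρ²);
- mean of the two later visits, unadjusted: v = 49(1 + ρ)/2;
- mean of the two later visits, baseline-adjusted: v = 49[(1 + ρ)/2 − ρ²];
- reading (b), mean over three visits: effect (0 + 5 + 5)/3 = 3.33, v = 49(1 + 2ρ)/3;
- reading (c), group-by-time: noncentral F on 2 and 140 df with λ = 18 × Σ(d − d̄)²/[49(1 − ρ)], where d is the group difference at each visit.

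For effects 0, 5, 5, Σ(d − d̄)² = 3.33² + 2 × 1.67² = 16.67. At ρ = 0.5, λ = 18 × 16.67/24.5 = 12.24.

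**Power, effect 5 at both later visits**

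| Analysis | ρ 0.3 | ρ 0.5 | ρ 0.7 | ρ 0.8 |
|---|---|---|---|---|
| (a) one later visit, unadjusted | 0.85 | 0.85 | 0.85 | 0.85 |
| (a) mean of later visits, unadjusted | 0.96 | 0.93 | 0.90 | 0.88 |
| (b) group main effect, three visits | 0.78 | 0.68 | 0.61 | 0.57 |
| (c) group-by-time | 0.75 | 0.88 | 0.985 | 0.999 |
| One later visit, baseline-adjusted | 0.88 | 0.93 | 0.99 | 0.999 |
| Mean of later visits, baseline-adjusted | 0.98 | 0.99 | 0.999 | >0.999 |

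**Power, waning effect (5, then 2.5).** Here Σ(d − d̄)² = 2.5² + 2.5² + 0² = 12.5, and the later-visit mean effect is (5 + 2.5)/2 = 3.75.

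| Analysis | ρ 0.3 | ρ 0.5 | ρ 0.7 | ρ 0.8 |
|---|---|---|---|---|
| (c) group-by-time | 0.62 | 0.77 | 0.94 | 0.99 |
| Mean of later visits, baseline-adjusted | 0.85 | 0.89 | 0.96 | 0.99 |
| 8 weeks only, baseline-adjusted | 0.88 | 0.93 | 0.99 | 0.999 |

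The fair comparator for (c) is the adjusted mean of the two later visits, because both use the whole follow-up. The 8-week row owes part of its advantage in the second table to picking the more favourable visit.

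**The case against.** The strongest reply is that the text leans towards reading (c). The Data analysis section plans intergroup effect sizes to convey the size of change, and the Discussion speaks of differences in improvement. Both suggest a between-group comparison of change, which in a repeated-measures model is the group-by-time term. That term uses baseline, removes chance imbalance and dilutes nothing. At ρ of 0.8 it gives up almost nothing. A condensed article may also leave the tested term to the full protocol or analysis plan. All of this stands.

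A reader might infer more than the article supports:

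- *Baseline QoL is thrown away and the effect is diluted.* These cannot both happen. Baseline is unused only under (a), and dilution to 3.3 arises only under (b), the reading with least support in the text.
- *The strongest predictor is ignored.* This is plausible, but the article gives no correlation to show it.
- *No estimate at 8 weeks will be produced.* This is not shown. The model can yield adjusted means by visit, and an article need not list its output tables.
- *The decision should rest on 8 weeks.* The Objectives section targets both the immediate and the long-term effect, so the article does not support dropping the later visit.

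What the reply does not answer is the covariate list. It is stated, not left open, and it omits a pre-randomisation measurement of the outcome.

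**Conclusion.** The concern holds as a matter of efficiency and clarity. The stated model has four covariates without baseline QoL, and the article settles neither the role of the baseline visit nor the tested term. With 36 per arm, SD 7, two-sided 0.05, a sustained 5-point effect and an assumed ρ of 0.3 to 0.8, the cost is:

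- (a) single-visit power of 0.85, against 0.88 to 0.999 with adjustment;
- (b) an effect of 3.3 in place of 5, with power of 0.78 falling to 0.57;
- (c) power of 0.75 to 0.999, against 0.98 to above 0.999 for the adjusted mean of the later visits.

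Under (c), the likeliest reading, the loss is material at low to moderate correlation: 0.75 against 0.98 at ρ 0.3 with a sustained effect, and 0.62 against 0.85 with a waning one. At ρ of 0.7 to 0.8 it is small or nil. The size therefore rests on a correlation that the article does not report.

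It would be wrong to infer bias. Allocation is randomised, and each reading gives a valid test.

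**What to change.** Take the 8-week and follow-up scores as outcomes in a longitudinal model with baseline QoL as a covariate, together with group, visit, group-by-visit and the four covariates already listed. Report the adjusted group difference in points, with its 95% CI, at 8 weeks and at follow-up, alongside the planned effect sizes. Before the data are examined, the sponsor should name the contrast that decides the trial (8 weeks, follow-up or their mean), consistent with an objective that covers both the immediate and the long-term effect. Use the same form for the secondary outcomes, each with its own baseline value.

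The change is to wording only. The baseline data are already scheduled, no visit or patient is added, and the model spends one further degree of freedom.

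### Repeated-measures ANCOVA, as named, does not ensure the promised intention-to-treat analysis: in its classical form a woman who misses the last visit also loses her observed 8-week score

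*Protocol article*

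**What the plan says.** The Data analysis section of the protocol article fixes the main method: "The main analysis will be repeated measures analyses of the covariance (ANCOVA) with age, type of surgery, tumour stage and time since diagnosis as covariates". It then makes a general commitment: "We will use the intention-to-treat principle for all analyses". On software it says "All analyses will be carried out using STATA/SE 14.0 StataCorp, College Station, TX, USA) or using Statistical Program for Social Sciences", without naming a procedure in either package.

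The Research design and methods section sets three visits: "assessments at baseline and immediately after the 8-weeks intervention", and then "Follow-up measurements will be collected for 24 weeks after the end of the 8-week intervention period", which is week 32. The Objectives section makes both the immediate and the long-term effect on QoL part of the main objective.

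The Sample size section expects some women to be lost: "A maximum loss at follow-up of 10% will be allowed to face a possible drop-out rate". It sizes the trial on 36 per group and recruits 40 per group.

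The article does not say how a woman with a missed visit enters the repeated-measures model.

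**The concern.** Two commitments in the same section do not fit together unless the procedure is specified. Intention-to-treat calls for each randomised woman to be kept in her allocated arm and for her observed outcomes to be used. Classical repeated-measures ANCOVA, with one row per woman and one column per visit, needs every column filled. A woman seen at baseline and 8 weeks but absent at week 32 is removed from the whole model, so her 8-week score leaves the 8-week comparison because of something that happened up to 24 weeks later.

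The 8-week result is half of the main objective, and this loss of data is avoidable. It matters if the reasons for leaving are related to QoL and differ between arms. That is plausible here: one arm attends three supervised sessions a week for eight weeks, the other has the app and paper recommendations, and only the assessors are described as blinded. The set of women analysed would also depend on which of the two packages and procedures the analyst happens to use.

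**Working it through.** **Inputs from the article.** 40 randomised and 36 evaluable per arm, 10% maximum loss, SD about 7, target difference 5 (stated as 5%, read as 5 points), and three visits.

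**Assumptions not in the article.** Correlation between visits 0.6 (0.5 and 0.7 also tried); the way loss depends on the 8-week score; how loss splits between arms.

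**Step 1: the plan's own figure.** 36 / (1 − 0.10) = 40 per arm. This reproduces. Deleting 10% of women therefore leaves 40 × 0.90 = 36 per arm, or 8 of 80 women dropped, which is what the trial was sized for. At the planned rate there is no unbudgeted loss of power. (How 36 itself was obtained is a separate question: 2 × (7/5)² × (1.645 + 1.282)² gives 34 one-sided, and 2 × (7/5)² × (1.960 + 1.282)² gives 42 two-sided.)

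**Step 2: bias formula.** Suppose a proportion p of one arm is lost at week 32, and those women have an 8-week mean d points below their arm's mean, while loss in the other arm is random. The mean of the women who remain rises by p·d/(1 − p). Adjusting for baseline at correlation ρ removes part of this, leaving approximately

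bias ≈ −(1 − ρ²) × p·d/(1 − p).

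With p = 0.10 and ρ = 0.6, 1 − ρ² = 0.64 and p/(1 − p) = 0.111.

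**Step 3: numbers, and a check by simulation** (1,000,000 women per arm, true difference 5 at both follow-up visits, loss from the m-health arm depending on the 8-week score, integral loss random, 10% in each arm, 8-week difference adjusted for baseline):

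| Log-odds of loss per SD of 8-week QoL | d (points) | Formula | Simulated, completers | Simulated, all 8-week data |
|---|---|---|---|---|
| 0 (random) | 0 | 5.00 | 4.99 | 4.99 |
| −0.5 | 3.0 | 5 − 0.64 × 0.111 × 3.0 = 4.79 | 4.78 | 5.00 |
| −1 | 5.7 | 4.59 | 4.58 | 4.99 |
| −2 | 9.0 | 4.36 | 4.34 | 5.00 |
| exactly the lowest 10% leave | 12.3 | 4.13 | 4.07 | 4.99 |

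The last row is the worst case for this loss pattern. The range is therefore about 4.1 to 4.8.

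**Step 4: when there is no bias, and when it reverses.** If loss has a slope of −1 in both arms at equal rates, the completers' estimate is 4.99. If high scorers leave the m-health arm (slope +1), it is 5.41.

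**Step 5: sensitivity to the assumptions.** At slope −1 in the m-health arm only and 10% loss per arm, the estimate is 4.52 at correlation 0.5 and 4.69 at 0.7. If baseline is a level of the repeated factor rather than a covariate, the contrast is a difference in change, and (1 − ρ) = 0.4 replaces 0.64. The estimates are then 5 − 0.4 × 0.111 × 5.7 = 4.75 and, in the worst case, 5 − 0.4 × 0.111 × 12.3 = 4.45.

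**Step 6: what using all observed data does.** The 8-week estimate returns to about 5.0 in every row. For week 32, at slope −1 in the m-health arm only and 10% loss per arm, completers give 4.85 to 4.86 (correlations 0.5 and 0.7), and an analysis that also uses the observed 8-week scores under missing at random gives 5.00 to 5.01.

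**The case against.** The strongest case against the point is that the article names a family of methods and no procedure. Stata's long-format anova keeps a woman's observed visits, and both packages fit mixed models. This is also a journal article: a full protocol or SAP may settle how missed visits are handled, and silence on that is no fault. The intention-to-treat sentence can itself be read as a commitment to keep such women in.

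Much of this stands. A reader might infer that the named software will drop every woman with a missed visit, or that the plan breaks its intention-to-treat promise. The documents support neither, because deletion depends on a choice the article leaves open. What remains does not rest on silence: the method the article does name, in its classical form, conflicts with the principle it does state, and nothing in the section rules that form out.

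A second objection concerns size. The standard error of the difference at 36 per arm is 7 × √(2/36) = 1.65 points, or about 1.65 × √(1 − 0.36) = 1.32 after baseline adjustment, so a bias of 0.2 to 0.9 is below one standard error. That is correct. It is still a systematic error, set against a minimally important difference that starts at 5 points, and it can be avoided with data already collected.

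A third objection is that the direction is unknown. M-health women are offered the face-to-face programme only after the last outcome is measured, which gives them a reason to stay. This also stands, and no direction is claimed here.

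**Conclusion.** The point holds in a limited form. Naming repeated-measures ANCOVA does not ensure the promised intention-to-treat analysis, because its classical wide-format version discards the observed 8-week scores of women lost later. At the planned 10% loss this costs no power beyond what was budgeted.

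The 8-week estimate can be biased only if loss depends on QoL and differs between arms in mechanism or rate. With a true difference of 5 points and 10% loss per arm, it is about 4.1 to 4.8 if low-QoL women leave the m-health arm only. It lies above 5 if high-QoL women leave that arm, and at 5.0 if loss is random or alike in both arms. These figures rest on an SD of 7 from the article and on an assumed correlation of 0.6 and assumed loss mechanisms.

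A reader might also infer a larger distortion. Estimates of about 3.3 to 3.9 do arise, but only with strong selection combined with unequal loss (15% against 5%, or 20% against none). The article gives a single overall maximum of 10% and nothing by arm, so those figures should not be used as the size of the problem. This is a change worth making before analysis, not a flaw that invalidates the trial.

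**What to change.** In the Data analysis section, name as the main analysis a likelihood-based mixed model for repeated measures, fitted by REML:

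- outcome: the QoL score at 8 weeks and at week 32;
- fixed effects: group, visit, group by visit, baseline QoL, and the four covariates already stated;
- covariance: unstructured over the two follow-up visits;
- data: every observed follow-up score of all randomised women, analysed in the arm to which they were allocated;
- estimates: the group difference at each visit.

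Add one sensitivity analysis for data not missing at random, for example shifting the imputed scores of lost women in one arm over a range stated in advance. It should cover women with no follow-up score at all, since they contribute nothing to the main fit. If a fuller analysis plan already specifies such a model, the article's description of the main method should be brought into line with it.

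Both named packages can fit this model. The cost is a few sentences and modest programming, with no extra patients, visits or data. Per-visit ANCOVA on all observed scores, or multiple imputation, would also resolve the conflict, but the mixed model does so in one step and uses the 8-week scores to inform week 32.
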